### End Points

The primary endpoint is the DASH score 6 months after surgery. Secondary endpoints are listed in table 4.

**Table 4 T4:** Primary and secondary endpoints

Primary Endpoint	Secondary Endpoints
- DASH score after 6 months	- Constant Score after 6 months
	- DASH and Constant Score after 6 weeks, 3 months and 1 year
	- Complications: intra-operative, post-operative period (2 weeks) and after 6 weeks, 3 and 6 months and 1 year
	- Reoperation after unsatisfying result in a time horizon of 1 year (including implant removal)
	- Time to radiological consolidation, with a maximum time horizon of 6 months
	- Pain score, until 2 weeks postoperative
	- Cosmetic satisfaction after 6 months and 1 year

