### Follow-up

The patient is requested to record - on a daily basis during the fortnight immediately following surgery - the pain experienced as well as the type and amount of analgesics used. Experienced pain is assessed with a 10-point Likert scale (0 = no pain and 10 = extremely painful).

All patients are reviewed in the outpatient department by the treating surgeon and investigator at 2 and 6 weeks, 3 and 6 months and 1 year after surgery. All visits include standardized clinical evaluation and registration of possible complications by the treating surgeon and the investigator (table 3).

**Table 3 T3:** Complications

Intra-operative complications	Post-operative complications
- Nerve/vessel damage	- Wound healing disorders (infection, hypertrophic scar, dehiscence)
- Other operative complications	- Transient brachial plexus laesion (defined as paresthesia of the arm, and weakness of the pink and index finger)
	- Irritation of the implant (post-operative pain/itch/redness/irritation)
	- Migration of the implant
	- Breakage of the implant
	- Non-union (defined as lack of radiographic healing with clinical evidence of pain and motion at the fracture site after 6 months)
	- Mal-union (defined as union of the fracture in a shortened, angulated, or displaced position with weakness, easy fatigability, pain with overhead activity, neurologic symptoms, and shoulder asymmetry)
	- Other complications

At the 2 weeks outpatient visit the pain diary is discussed by the researcher with the patient. Radiographs will be taken in order to check implant position and, at subsequent follow-up visits until radiographic union. Radiographic union is defined as complete cortical bridging between proximal and distal fragments on both radiographs as determined by the treating surgeon.

The Disabilities of the Arm, Shoulder and Hand (DASH) and Constant scores will be gathered at the 6 weeks, 3 and 6 months and 1 year postoperative visits by the investigator [15-17].

The DASH questionnaire is a self administered region-specific outcome instrument developed as a measure of self-rated upper extremity disability and symptoms. The DASH questionnaire consists mainly of a 30-item disability/symptom scale, scored 0 (no disability) to 100 (= completely disabled upper extremity) [15,16]. To prevent bias, the DASH questionnaires will be completed in absence of the operating surgeon, before the clinical assessment.

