## Discussion

No comparative prospective or randomized study has been published comparing outcome of plate fixation with ESIN with a TEN of DMCF. The study aim is to provide and compare results of plate fixation and ESIN with a TEN.

Traditionally DMCF were treated conservatively. This policy was based on good results from large cohort series from the sixties: non union rates were < 1% [3,4].

These series, however, were all very mixed with regard to age, clavicular fracture site, displacement and fracture classification. Children, who have better bone healing and remodelling mechanisms, were also included. Malunion was not yet accepted as a clinical entity. Outcome was surgeon based contrary to present-day patient based outcome tools like DASH and Constant scores.

Surgical treatment however, has its own drawbacks. Wound healing disorders, infections, loss of fixation and nonunions do also occur as listed in table 3[12,13,19-22]. In addition, a second surgical procedure might be required to remove the implant. Nevertheless, recently published studies reporting lower nonunion rates, improved functional outcome, faster mobilization and (perhaps therefore) increased patient satisfaction initiated a tendency towards surgical treatment of DMCF [8,12,13,22].

Theoretically, both plate fixation and ESIN have their own advantages. A biomechanical study shows that plate fixation provides a more rigid stabilization compared to ESIN. Therefore plate fixation may provide a stronger construct for early rehabilitation protocols [23]. Plate fixation is technically easy to perform which provides another advantage.

On the other hand, ESIN is less invasive, results in lesser implant prominence and implant removal can be done with minimal dissection [22]. If closed reduction is possible, this technique has the advantage of an intact fracture hematoma, which could speed up the healing process. However, minimally invasive techniques exert certain specific risks that can lead to complications (e.g. for the clavicle iatrogenic brachial plexus injury have been described [20]). The primary endpoint of this study is the DASH score 6 months after surgery. After 6 months the nonunion rates can be calculated and therefore 6 months is the first possible endpoint to determine the success rate of the surgery. Patients will be followed for a 1 year period, mainly to asses the follow-up of nonunions or other implant-related complications.

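### The radiographic-union endpoint stops at 6 months, so no endpoint reports union at 1 year, although unhealed fractures are still imaged then

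*Protocol article*

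**What the plan says.** All references are to the protocol article.

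- **End Points, Table 4** lists as a secondary endpoint "Time to radiological consolidation, with a maximum time horizon of 6 months". The same table assesses complications up to 1 year and gives reoperation a 1-year horizon. DASH, Constant score and cosmetic satisfaction also have 1-year assessments.
- **Follow-up** sets the visits "at 2 and 6 weeks, 3 and 6 months and 1 year after surgery". On imaging it says: "Radiographs will be taken in order to check implant position and, at subsequent follow-up visits until radiographic union".
- **Follow-up** defines union by bone alone: "Radiographic union is defined as complete cortical bridging between proximal and distal fragments on both radiographs as determined by the treating surgeon".
- **Follow-up, Table 3** defines the complication non-union as "lack of radiographic healing with clinical evidence of pain and motion at the fracture site after 6 months".
- **Statistical Methods** assigns Kaplan-Meier analysis to time to consolidation.
- **Discussion** explains 6 months as the earliest time at which a nonunion rate can be worked out, and explains the longer follow-up: "Patients will be followed for a 1 year period, mainly to asses the follow-up of nonunions or other implant-related complications".

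**The concern.** Four statements do not sit well together. The trial follows patients for a year largely because of nonunion. It goes on taking radiographs of fractures that have not united. Yet it closes the union endpoint halfway through, and the one union-related outcome that runs to 1 year requires symptoms. The 1-year radiograph of a fracture still open at 6 months cannot change the union result.

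What is at stake is the interpretation of a secondary outcome. The Discussion counts radiographic union among the outcomes that make its assessment of efficacy complete, and gives reasons why the arms might heal differently: a more rigid construct with the plate, an undisturbed fracture haematoma when closed reduction with the nail succeeds. A 6-month cut describes how fast fractures heal up to that point. It does not say whether those still open then were slow or had failed.

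**Working it through.** There is no planned figure to reproduce, because the article gives no union, delayed-union or nonunion rate after either operation. The check is a comparison of the definitions, followed by an illustrative count.

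**Step 1. Is a late radiograph taken?** Imaging continues at follow-up visits until union, and the last scheduled visit is at 1 year. Read literally, every fracture not bridged at 6 months is imaged again at 1 year.

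**Step 2. What does each endpoint record?** The table takes Table 4's complication time points as status at each visit. Both signs means pain and movement at the fracture.

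| Course of the fracture | Union endpoint (to 6 months) | Table 3 non-union |
|---|---|---|
| A. Bridged by 6 months | Event | No |
| B. Bridges between 6 and 12 months, never both signs | Not consolidated at 6 months | No |
| C. Not bridged at 1 year, never both signs | Not consolidated at 6 months | No |
| D. Bridges between 6 and 12 months, both signs at 6 months | Not consolidated at 6 months | Yes at 6 months, no at 1 year |
| E. Not bridged at 1 year, both signs persist | Not consolidated at 6 months | Yes at 6 months and 1 year |

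The union endpoint treats B, C, D and E alike. The complications endpoint separates D from E, and reoperation adds information to 1 year. B and C are the same in both columns, although the 1-year radiograph tells them apart. This is the gap.

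**Step 3. How many patients?** Inputs: N = 120 (Sample Size and Power); u = proportion unhealed at 6 months; v = proportion of those that bridge by 1 year. Both u and v are assumptions.

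- Unhealed at 6 months = N × u
- Late unions = N × u × v
- Still unhealed at 1 year = N × u × (1 − v)

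| u | Unhealed at 6 months | Late unions, v = 25% to 75% | Still unhealed at 1 year, v = 25% to 75% |
|---|---|---|---|
| 2% | 120 × 0.02 = 2.4 | 0.6 to 1.8 | 1.8 to 0.6 |
| 5% | 120 × 0.05 = 6 | 1.5 to 4.5 | 4.5 to 1.5 |
| 10% | 120 × 0.10 = 12 | 3 to 9 | 9 to 3 |
| 15% | 120 × 0.15 = 18 | 4.5 to 13.5 | 13.5 to 4.5 |

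These counts ignore symptoms. Patients in courses D and E are among them, so the number in B and C is smaller still.

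**The case against.** The strongest reply is that the cap is reasoned. The Discussion treats 6 months as the point from which nonunion can be judged, and Table 3 uses the same threshold. On that view, time to consolidation runs up to the threshold, and complications and reoperation take over to 1 year. The Discussion speaks of following nonunions and implant-related complications and does not promise a union proportion at 1 year. Non-union as the protocol defines it is indeed followed, so there is no outright contradiction. The radiographs will also be on file and could be reported descriptively in any case.

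Most of this stands, and it limits what can be claimed. Three stronger readings are tempting and are not supported:

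- *Symptom-free unhealed fractures are lost to every endpoint.* They are not. Union is defined without symptoms, so they enter the Kaplan-Meier analysis as unconsolidated at 6 months and lower that arm's consolidated proportion. Only their later status is missing.
- *The trial cannot tell delayed union from nonunion.* Symptomatic non-union is assessed again at 1 year, and the radiographs that would separate the remaining cases are taken. The limitation lies in the union endpoint, not in the data.
- *A 6-month radiograph taken a few days late falls outside the horizon.* No text says so, and visit windows are detail that an article may leave to the full protocol.

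The reply does not remove the gap. Calling 6 months the earliest usable time justifies a read-out then; it does not justify ending there. Reporting the 1-year radiographs only descriptively is also weaker than planning it. The trial is unblinded and the treating surgeon judges union, so a 1-year comparison chosen after the results are seen would be open to challenge.

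**Conclusion.** The point holds in a limited form. Table 4 ends the union endpoint at 6 months and Table 3 non-union requires symptoms, so no endpoint gives radiographic union at 1 year, although unhealed fractures are imaged then and nonunion is a stated reason for the longer follow-up. Within the union endpoint, slow and failed healing look the same.

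The number affected is unknown. The assumed range of 2% to 15% gives about 2 to 18 of 120 patients unhealed at 6 months. The lower part is more plausible, since the Background reports less nonunion after surgery than after conservative treatment, but it gives no figure. With so few patients, a 1-year comparison would be descriptive. The conclusion rests on reading the imaging rule literally, so that the 1-year radiograph is taken when union has not yet been seen. The 6-month DASH comparison, sample size and alpha are not touched. This is a worthwhile improvement to a secondary endpoint and not a flaw in the trial's main inference.

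**What to change.** In Table 4, let time to radiological consolidation run to the 1-year visit and keep the 6-month estimate as a stated read-out. Add, by arm, the proportion without radiographic union at 6 months and at 1 year regardless of symptoms, shown beside the symptomatic non-union of Table 3.

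There is only one scheduled visit after 6 months, so the Kaplan-Meier curve would mostly gain a single step at 1 year. The two proportions will therefore carry most of the added information. The plan should also state how a fracture reoperated on before bridging is counted.

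The cost is one changed line and one added pair of proportions, fixed before outcome data are compared by arm. No visit, radiograph or aspect of patient care changes.

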### Implant removal

Implant removal is scored as a re-operation if it occurs within the first 6 months and is due to implant related problems (listed in table 3).

Implant removal according to the patient's wish will be granted after consolidation.

### Safety measures

Surgeons operating patients for this study must have extensive experience with both plate fixation and ESIN with a TEN. It is assumed that every surgeon must have performed over 20 procedures in both techniques to operate on patients who participate in this study. The cut-off value of 20 operations is established on personal experience by one of the authors ([name]), who participated in the Content-study in which conservative treatment of DMCF was compared to ESIN with a TEN (results not published yet). In this study the learning curve for ESIN with a TEN was passed after 20 procedures.

### Sample Size and Power

The primary outcome measure in this study is the DASH score. Initially, a minimum difference of 10 points in DASH score can be considered as clinically relevant [16]. However the DASH score rates the whole upper extremity and a smaller difference should be considered as clinically relevant when focusing on clavicular function in particular.

Unfortunately, no studies comparing plate fixation and ESIN for dislocated midshaft clavicular fractures with power calculation are available [14]. Therefore we performed a power calculation based on the following rationale. A DASH score of a "normal" upper extremity varies between four and eight [15]. The DASH score of the group of patients who were conservatively treated for DMCF after 24 weeks was 14 [12]. We consider the difference of six points between this latter DASH score and the worst score (eight) within the normal range as the clinically relevant margin. This coincides well with a recently online published protocol for treatment of wrist fractures in which a comparable margin in DASH score for local function (five points) is considered clinically relevant (Design Minimax studie: http://www.cruamc.nl/Minimax). With an expected standard deviation of 11 points in the DASH score, a two sided alpha of 0.05 and a power of 0.80, 53 patients in each group are needed (total 106) to show a difference of at least 6 points in DASH score after 6 months. Considering that an interim analysis is planned (see below), it is assumed that 2 sequential tests are made using the O'Brien-Fleming spending function to determine the test boundaries. Further assuming a 10% loss to follow-up, 120 patients should be included.

### Statistical Methods

Data will be analyzed according to the intention-to-treat principle. The difference between the operative techniques at the end of the follow-up period in DASH (primary outcome) and Constant scores will be tested for significance using the Student's T-test or the Mann-Whitney U test, depending data distributions. A general linear random effects model will be applied to assess differences during the follow-up period in DASH, Constant, pain, and SF-36 scores to account for repeated measures within patients. The difference in the frequency of complications during follow-up will be assessed with Poisson regression, whereas the Chi-square test or Fisher's exact test will be used to test for differences in proportion of re-operated patients. Differences in cosmetic satisfaction will be tested using the Mann-Whitney U-test. Time to radiological consolidation will be assessed by Kaplan-Meier analysis. A p-value of < 0.05 will be considered statistically significant in all analyses. SPSS software will be used for statistical analysis.

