**Methods/Design:**

Prospective randomized multicenter clinical trial in two level 1 and one level 2 trauma centers. 120 patients between 18 and 65 years of age will be included. They are randomized to either plate fixation or ESIN with a TEN with a one year follow-up. Sixty patients will be treated with plate fixation and 60 patients will be treated with ESIN. Primary outcome parameter is the Disabilities of the Arm, Shoulder and Hand score after 6 months. Secondary outcome parameters are Constant Shoulder Score, complications, experienced pain, radiologic consolidation and cosmetics after both procedures.

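### The primary DASH test is written for the end of follow-up (1 year), while the primary endpoint and the sample size are set at 6 months

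*Protocol article*

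**What the plan says.** **The test.** The Statistical Methods section of the protocol article gives the between-group test of the primary outcome in one sentence: "The difference between the operative techniques at the end of the follow-up period in DASH (primary outcome) and Constant scores will be tested", by t-test or Mann-Whitney test depending on the distribution. The only other DASH analysis in that section is a random effects model for differences over the course of follow-up. That model names no visit and is not called primary.

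**The endpoint.** The Abstract says: "Primary outcome parameter is the Disabilities of the Arm, Shoulder and Hand score after 6 months". End Points says: "The primary endpoint is the DASH score 6 months after surgery". The Discussion repeats this and gives a reason: nonunion can first be assessed at 6 months. Among the secondary endpoints, Table 4 lists "DASH and Constant Score after 6 weeks, 3 months and 1 year".

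**The sample size.** Sample Size and Power calculates the number of patients needed "to show a difference of at least 6 points in DASH score after 6 months".

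**The length of follow-up.** The Abstract says: "They are randomized to either plate fixation or ESIN with a TEN with a one year follow-up". The Discussion says: "Patients will be followed for a 1 year period". The last visit in the Follow-up section is at 1 year after surgery.

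**The interim.** The section on the data and safety monitoring board places the interim analysis after one year. It describes the DASH stop criterion as the first of two sequential tests of the primary outcome, and names no visit.

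**The concern.** The document ends follow-up at 1 year. The Statistical Methods sentence therefore labels as primary a comparison that Table 4 classes as secondary, and no sentence names a between-group test at the 6-month visit. An analyst who followed the section literally would compute the primary p-value at a visit other than the one for which the trial was sized.

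The group-sequential design is affected too. Two sequential tests share one type I error only if both examine the same outcome. If the final test uses the 1-year DASH, the interim test of the primary outcome has to use the same variable, and at that date it is practically unavailable.

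**Working it through.** **1. What the end of follow-up means here.** Three places give the length of follow-up: the Abstract (one year), the Follow-up section (last visit at 1 year) and the Discussion (1 year). None gives 6 months. The Statistical Methods section itself uses follow-up for the whole period when it covers repeated measures and complications. The phrase in the primary-test sentence therefore denotes the 1-year visit.

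**2. The statements side by side.**

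| Place in the protocol article | Time point for DASH |
|---|---|
| Abstract, Methods/Design | 6 months, primary |
| End Points and Table 4 | 6 months, primary; 1 year, secondary |
| Sample Size and Power | 6 months |
| Discussion | 6 months, primary |
| Statistical Methods | end of follow-up (1 year), labelled primary |
| Interim criterion | no visit stated; refers to the primary outcome |

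**3. Which time point the sample size belongs to.** Inputs from Sample Size and Power: difference 6 points, SD 11, two-sided alpha 0.05, power 0.80.

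- n per arm = 2 × (1.960 + 0.842)² × 11² / 6² ≈ 52.8, rounded up to 53. This reproduces the stated 53 per arm and 106 in total. The t-test version gives 53.7, so 54; at 53 per arm the power is 0.802 by the normal formula and 0.794 by the t-test.
- 10% loss: 106 / 0.90 = 117.8, so 118. With an assumed inflation factor of about 1.008 for two O'Brien-Fleming looks, 53 × 1.008 = 53.4, so 54 per arm and 108 in total; 108 / 0.90 = 120. This matches the stated 120.

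These figures are tied to the 6-month score. The document gives no difference, SD or power for the 1-year DASH.

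**4. Whether a 1-year outcome can be tested at the interim.** The interim takes place after one year, when 72 patients are expected to have been included. A 1-year score falls due 12 months after surgery, and surgery follows randomization. Even the earliest patients would therefore only be approaching that visit.

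- With a 1-year DASH: practically 0 of 72.
- With a 6-month DASH: about 36 of 72, assuming even accrual (72 × 6/12). The protocol expects recruitment to speed up, so the true number could be lower.

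The interim effect size of 0.55 agrees with the sample-size assumption (6 / 11 = 0.545). That is consistent with both concerning the same score, although it does not name a visit.

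**The case against.** **This is a drafting slip with an obvious reading.** Several explicit statements fix 6 months, the Discussion gives a reason for it, and the test sentence itself refers to the primary outcome. A reader can reasonably suppose that 6 months was meant, and the published endpoint table leaves little room to switch later. This stands as a view of intent. It does not remove the contradiction, because the one sentence that prescribes the test gives a different time point. Nor is this an omission that an unseen analysis plan could fill, since the article states a time point and it conflicts with the endpoint.

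**The random effects model covers 6 months.** It does use the 6-month data. It is not designated as the primary analysis, however, and no contrast at 6 months is specified.

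**Stronger readings that the documents do not support.**

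- A reader might infer that the interim boundary is explicitly defined at 6 months. It is not; the link runs through the reference to the primary outcome.
- A reader might infer a definite loss of power at 1 year, because the arms could converge. The documents give neither a 1-year difference nor a 1-year SD. Any such figure would reflect the assumed values, and a smaller SD could offset a smaller difference.
- A reader might infer a definite inflation of the type I error from choosing between two visits. That would need a correlation between visits, which is not given.
- A reader might infer that the 6-month Constant score ranks above the other secondary endpoints. Table 4 lists it first but states no hierarchy, so a 1-year Constant test is also a test of a listed secondary endpoint.

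**Conclusion.** The Statistical Methods sentence is wrong as written. It puts the primary test on the 1-year DASH, a secondary endpoint with no power calculation. It also cannot be reconciled with a first sequential test after one year, when practically no patient can have that score. The defect concerns which visit carries the primary p-value, so it should be corrected before any comparison between arms.

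Its size is qualitative. The sample-size figures were calculated for 6 months and need no change, and no percentage loss of power can be derived from the documents. The conclusion on the time point rests on the document's own definition of follow-up. The interim argument also takes the interim to fall one year after recruitment starts, as the expected 72 inclusions imply. The count of about 36 patients with a 6-month score additionally assumes even accrual. Whether the analysis would in fact have been run at 1 year cannot be judged from this article.

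**What to change.** - **Statistical Methods, primary test:** replace the reference to the end of follow-up with 6 months after surgery for the DASH.
- **Statistical Methods, Constant score:** name 6 months in the same way for the 6-month Constant score.
- **Statistical Methods, 1-year scores:** state that the 1-year DASH and Constant comparisons are secondary, as Table 4 already has them. Say whether they are tested the same way or through the random effects model, so that they are not left without a named analysis.
- **Interim analysis:** state that the DASH criterion uses the 6-month score.

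The cost is a few words in two sections. Recruitment, visits, data collection and the sample size of 120 are unchanged.

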### Intake

Ultimately within 1 week, an appointment with an orthopedic trauma surgeon and the investigator will take place. If informed consent is obtained, the patient is included in the study, patient data are obtained by the investigator (table 2) and the patient is randomized.

**Table 2 T2:** Preoperative data

Preoperative data	
- Age	- Smoking
- Gender	- Medical history
- Dominant arm	- Medication
- Trauma mechanism (sports, traffic accident, etc)	- SF-36 Questionnaire [18]
- Sports (if yes; at what level? Recreational or professional)	- Body Mass Index
- Occupation	- AO Classification of fracture *

* this classification exactly concurs to the OTA classification of midshaft clavicular fractures

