The Constant score includes an analysis of pain, shoulder motion, strength, and function. From a perfect score of 100, it reserves 35 points for patient-reported subjective assessment, including the presence of pain and the ability to perform basic activities of daily living, and 65 points for objective measurement. For the latter, 40 points are allocated to range of motion and 25 points are allocated to strength [17].

The cosmetic result after 6 weeks, 3 and 6 months, and 1 year is assessed by eliciting a patient satisfaction score on a 0 (= very unsatisfactory) to 10 (= very satisfactory) Likert scale.

After 6 months and 1 year the patient is asked to complete the SF 36 questionnaire again (see table 2) [18]. The SF 36 is a validated questionnaire designed to measure health related quality of life.

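### The SF-36 is collected before randomisation, but the stated random effects model gives that score no role, so the quality-of-life comparison is less precise than the collected data allow

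*Protocol article*

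**What the plan says.** In the Intake section, the order of events once consent is given is that "patient data are obtained by the investigator (table 2) and the patient is randomized". Table 2, the list of preoperative data, includes the SF-36. The baseline value is therefore obtained before allocation is known.

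The Follow-up section repeats the same instrument: "After 6 months and 1 year the patient is asked to complete the SF 36 questionnaire again". There are thus one pre-randomisation score and two follow-up scores per patient.

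The Statistical Methods section deals with the SF-36 in one sentence shared with three other outcomes, which applies a general linear random effects model to "differences during the follow-up period in DASH, Constant, pain, and SF-36 scores to account for repeated measures within patients". The stated purpose is thus to handle the correlation of scores from the same patient. No covariate is named for any of the four outcomes, and none is excluded.

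Table 4 lists the primary and secondary endpoints. The SF-36 is not among them, although the Discussion counts quality of life as part of the overall efficacy assessment.

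**The concern.** One model sentence serves four outcomes with different data structures. DASH and Constant scores are first gathered at 6 weeks, and the pain diary covers the first two weeks after surgery, so none of these three has a pre-operative value. A model of post-surgical scores uses everything there is for them. The SF-36 is the exception: it has a true pre-randomisation measurement that the sentence does not use.

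What is at stake is precision. If the baseline predicts the later scores, leaving it out makes the standard error of the arm difference larger than it need be, in a trial with about 54 evaluable patients per arm (60 less 10%). Treatment is unblinded and the SF-36 is self-reported, so a decision on adjustment is also easier to defend if it is written down before outcome data are analysed.

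**Working it through.** **The plan's own figure.** The only sample size calculation is for DASH at 6 months: difference 6, SD 11, two-sided alpha 0.05, power 0.80. Then n per group = 2 × (1.960 + 0.842)² × (11/6)² = 52.8, which rounds up to 53, or 106 in total, as stated. Dividing by 0.90 for loss to follow-up gives 118, or 119 with an assumed inflation of about 1.008 for the O'Brien-Fleming interim look, against the stated 120. This reproduces, and the SF-36 point does not touch it. The article gives no effect, SD or power for the SF-36.

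**Inputs for the SF-36.**
- Three measurements per patient: intake, 6 months, 1 year (Table 2 and Follow-up section).
- Correlation r between the two follow-up scores: not given; assumed 0.5.
- Correlation ρ between baseline and each follow-up score: not given; assumed 0.2, 0.3 or 0.5.
- Equal variance at each time, scaled to 1.

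**Formulas.** For the mean of the two follow-up scores:
- variance without baseline: (1 + r)/2 = (1 + 0.5)/2 = 0.75;
- covariance of that mean with baseline: ρ;
- variance after adjustment for baseline: 0.75 − ρ².

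The variance of the arm difference is 2/n times these quantities, so their ratio does not depend on n.

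For illustration, take an effect that the unadjusted model would detect with 80% power. Adjusted power is then Φ(2.802/√ratio − 1.960). The 80% is an anchor chosen here and is not a figure from the plan.

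| ρ | Adjusted variance | Ratio to 0.75 | Reduction | Power (from 80%) |
|---|---|---|---|---|
| 0.2 | 0.75 − 0.04 = 0.71 | 0.947 | 5% | 82% |
| 0.3 | 0.75 − 0.09 = 0.66 | 0.880 | 12% | 85% |
| 0.5 | 0.75 − 0.25 = 0.50 | 0.667 | 33% | 93% |

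**Sensitivity.** With r = 0.7 the unadjusted variance is 0.85, and the ratios become 0.81/0.85 = 0.95, 0.76/0.85 = 0.89 and 0.60/0.85 = 0.71.

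**One visit alone.** The ratio is 1 − ρ²: 0.96, 0.91 and 0.75. With 54 patients per arm, the difference detectable with 80% power is 2.802 × √(2/54) = 0.539 SD without adjustment. Multiplying by √(1 − ρ²) gives 0.528, 0.514 and 0.467 SD.

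**Where ρ is likely to lie.** The baseline comes from the intake visit, timed as follows: "Ultimately within 1 week, an appointment with an orthopedic trauma surgeon and the investigator will take place". The patient has a recent, untreated fracture at that point, so the score may largely reflect the acute injury. That makes a low ρ, and hence the first rows of the table, plausible. The documents cannot settle it.

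**The case against.** The strongest reply is that the article is silent on covariates, not opposed to them. It is a condensed account, the model sentence names no covariate for any outcome, and a random effects model described this way is compatible with baseline adjustment. A covariate list is the sort of detail that often sits in a fuller document. A reader might therefore infer that the plan discards the baseline, but the text does not say so. It gives the score no stated role, and that is as far as the documents go.

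This limits the point without removing it. The sentence does fix a window, the period after surgery, and that window suits the three outcomes without a baseline better than it suits the SF-36. Adding the covariate is a concrete improvement that uses data already collected.

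A reader might also infer that the intake score would enter as a third repeated outcome under one common arm effect. That would average the effect over a time when the arms cannot yet differ and so dilute it. The documents do not support this reading: no such model is described, and the restriction to the follow-up period argues against it.

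Nor is there bias. Under randomisation the unadjusted comparison is unbiased, and its standard error already allows for chance baseline imbalance. Counting that imbalance as a further harm would count the same loss of precision twice.

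The remaining objections stand and bear on weight: the SF-36 is not a Table 4 endpoint, the trial was not sized on it, and the gain may be small.

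**Conclusion.** The point holds as a low-severity, cost-free improvement. The SF-36 is measured before randomisation and the stated analysis gives that measurement no role. As written, the comparison is valid but less precise than the data allow. With an assumed follow-up correlation of 0.5 and baseline correlations of 0.2 to 0.5, adjustment lowers the variance of the average arm difference by about 5% to 33%. The lower end is quite possible because of the timing of the baseline, and as ρ approaches zero the gain vanishes. The effect is confined to a supporting outcome. The primary DASH comparison, for which no baseline is collected, the sample size and the interim stopping criteria are unaffected.

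**What to change.** In Statistical Methods, separate the SF-36 from the other three outcomes and state that:
- the 6-month and 1-year SF-36 scores are the outcomes of the random effects model;
- the pre-operative score of the same SF-36 scale is a covariate;
- the arm difference is estimated at each of the two visits.

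The cost is a sentence or two of analysis wording, with no new data and no change to the sample size. Patients without an intake SF-36 need a simple rule, such as mean imputation of the baseline covariate. At the time of the article 25 patients had been included, so the choice could be fixed before outcome data are analysed.
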